## Abstract

**Background:**

Osteoarthritis is a relatively common musculoskeletal disorder that increases in prevalence with age. Worldwide, knee osteoarthritis is one of the leading causes of disability, particularly in the elderly. In numerous trials of agents for long-term pain therapy, no well-established and replicable results have been achieved. Complementary and alternative medical approaches have been employed for thousands of years to relieve knee osteoarthritis pain. Among herbal medicines, the golden plaster is the preferred and most commonlyused method in China to reduce pain in patients with knee osteoarthritis, as it causes few adverse effects. The purpose of this study will be to evaluate the efficacy and safety of golden plaster on pain in patients with knee osteoarthritis.

**Methods/Design:**

This study will be a multicenter randomized, double-blind, placebo-controlled trial. A total of 320 participants aged 45 to 79 years with knee osteoarthritis, whose scores on a visual analog scale (VAS) are more than 20 mm,will be randomly allocated into a treatment group and a control group. A golden plaster will be administered externally to participants in the treatment group for 2 weeks, while the control group will receive a placebo plaster externally for 2 weeks. Follow-up will be at regular intervals during a 4-week period with a VAS score for pain, quality of life, and complications.

**Discussion:**

This study will be a methodologically sound randomized controlled trial to assess pain relief after the intervention of golden plaster, compared to a placebo intervention in patients with knee osteoarthritis.

**Trial registration:**

ClinicalTrials.gov identifier: ChiCTR-TRC-13003418

## Background

Osteoarthritis (OA), a progressive joint disorder, is a common health issue in the aging population worldwide [1,2]. The prevalence rate of OA is 28% in people over 45 years old and 37% in people over 65 years old [3]; thus, its prevalence and health impact increase with age. Knee OAis one of the leading causes of disability, particularly in the elderly. The aim of OA treatmentisto reduce or control pain, improve physical function, prevent disability, and enhance quality of life. The non-surgical management of OA, namely pharmacologic treatment combined with physical therapy, is utilized more and more widely [4,5]. Pharmacologic treatments include oral analgesics, acetaminophen, ibuprofen, and traditional Chinese medicinal (TCM) products [6,7]. Several systematic reviews have outlined and showed the effectiveness of muscle strengthening or aerobic exercises in the osteoarthritic population [8-11]. Acupuncture and Tuina, two kinds of the physical therapy, have also been used for the management of OA [6,7]. Despite numerous trials, investigators have not been able to establish replicable relief of long-term pain.

Complementary and alternative medicine has been employed over thousands of years to relieve knee OA pain. Plasters are a very important therapeutic method in TCM, inducing muscle relaxation, invigorating blood circulation, and improving electrolyte balance and bile release [12,13]. Among herbal medicines, the golden plaster is the preferred and most commonly used method in China for pain reduction in patients with knee OA, as they cause very few adverse effects. Due to the absence of a gold standard for the treatment of knee OA, this trial will be conducted to detect the effectiveness of these herbal medicines compared to a placebo-controlled group. Therefore, we designed a randomized, double-blind, placebo-controlled trial of golden plaster in patients with knee OA.

## Methods/Design

### Study design

This clinical trial will be a multicenter, randomized, double-blind, placebo-controlled trial. Subjects will be enrolled at four hospitals: i) Suzhou Hospital of TCM; ii) Longhua Hospital affiliated to Shanghai University of TCM; iii) Zhangjiagang Hospital of TCM; and iv) Taizhou Hospital of TCM.

The Ethics Boards of the Suzhou Hospital of TCM, Longhua Hospital affiliated to Shanghai University of TCM, Zhangjiagang Hospital of TCM, and Taizhou Hospital of TCM have approved this study. Each participating center has obtained local Institutional Review Board approval. All study participants will sign the written informed consent before participation.

### Inclusion criteria

The inclusion criteria are as follows: age 45 to 79 years; symptomatic knee OA with a pain of at least 20 mm on a 100-mm visual analog scale (VAS); American College of Rheumatology criteria for symptomatic knee OA assessed by a rheumatologist [14]; ability to read, speak, and understand English or Chinese; and capability of understanding the study requirements and willingness to cooperate with the study instructions.

### Exclusion criteria

Exclusion criteria are as follows: psoriatic arthritis; lupus or cancer; severe cardiac or renal impairment; significant trauma to knees, including arthroscopy or significant injury to ligaments or the menisci of the knee within one year preceding the study; allergy to plaster.

### Recruitment

Participants will be recruited through advertisements in local newspapers, bulletin boards, and on the websites of local medical centers. All patients will be screened initially by baseline assessment with regard to selection criteria before randomization. If inclusion criteria are met and the informed consent form is signed, the patient will be sent to randomization.

### Randomization

The teletherapist, a research nurse, will then register the participant into the database for randomization. If the participant is ready to be randomized, the teletherapist enters “yes”; the site-specific randomization program behind the form displays the participant’s group assignment number (placebo versus golden plaster). Site-specific randomization lists will be computer-generated (i.e., generated by an individualized basic visual code program) and concealed from the researchers by a senior data manager who is not involved in the study. This information will remain confidential and is not shared with the study sites, in accordance with the CONSORT guidelines. This trial uses a prospective, randomized, outcome-blinded design, in which all outcome assessments are made by a research assistant blinded to treatment allocation and uninvolved in patient consent and management.

### Intervention

This study will be conducted in accordance with the requirements outlined in the Declaration of Helsinki, and approved by the appropriate Institutional Review Boards. Each participant will sign the written informed consent form before undergoing any examination or study procedure, in compliance with Good Clinical Practice. Eligible patients will be randomized into one of the two groups: placebo and golden plaster. All drugs will be administered externally for 2 weeks. Participants are given in-person instructions for using the plaster by our research nurses, who will be trained before this study. The trial will be double-blind: the treating physicians, subjects, investigators and statisticians are unaware of treatment assignment. Randomization of subjects will occur centrally using a random number generator. Patientvisitswill be performed at base line, and 1-, 2-, 3-, and 4-week follow-up after treatment (Figure 1). Assessments will be made during all five visits. Used plasters will be reclaimed at the 1- or 2-week follow-up visit.

**Figure 1 F1:**
[figure not shown]
Study flow diagram, including recruitment, eligibility, screening, randomization, and outcome assessments.

The investigational group will receive one medicated plaster, to be used twice a day (morning and evening, approximately every 12 hours and at the same time each day) for 14 consecutive days. The golden plaster is a 10 × 15 cm medicated adhesive patch, composed of Trichosanthes root, turmeric, angelica, Atractylodes, licorice, rhubarb, Phellodendron, Arisaema, Magnolia bark, tangerine peel, sesame oil, Huang Dan, and a hydrophilic adhesive vehicle.

The control group will receive placebo plasters (containing the hydrophilic adhesive vehicle only), which are identical to the tested formulation in terms of texture, size, color, and odor. The tested products will be packed and labeled, according to current Good Manufacturing Practice and legal requirements, by the Suzhou Hospital of TCM to ensure the participants and all personnel involved in the study will remain fully blinded as to the identity of the treatment administered. During the process, patients will not be allowed to use other drugs. If they do so, patients are required to provide feedback to the investigators and discontinue involvement in the study.

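### The ban on other drugs has no stated limit and makes users leave the study, although the entry criteria admit patients aged 45 to 79 with non-severe comorbidity and name no medication criterion

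*Protocol article*

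**What the plan says.** The rule stands in the protocol article under Intervention, in the text after Figure 1: "During the process, patients will not be allowed to use other drugs". The next sentence gives the consequence for patients who do: "patients are required to provide feedback to the investigators and discontinue involvement in the study".

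The entry criteria are broad. Inclusion criteria begin "The inclusion criteria are as follows: age 45 to 79 years" and end by asking for "willingness to cooperate with the study instructions". Exclusion criteria list psoriatic arthritis, lupus or cancer, "severe cardiac or renal impairment", recent significant knee trauma, and allergy to plaster. Neither list has a criterion on current medicines, washout or stable dosing.

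Under Recruitment, the article says: "All patients will be screened initially by baseline assessment with regard to selection criteria before randomization".

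**The concern.** The rule and the entry criteria do not fit together as written. The criteria let in middle-aged and older patients whose cardiac or renal disease is not severe, and they do not ask what medicines a patient takes. The rule then bars every drug other than the trial plaster and ends participation for anyone who uses one.

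Safety is at stake first. A willing patient could comply by stopping a needed medicine that has nothing to do with the knee, for the sake of a two-week trial of a plaster for pain. Recruitment and retention are at stake second: other patients would decline entry, or be enrolled and later removed, for a reason unrelated to knee pain. Consistency is a third issue. With four hospitals, one site could read the rule literally and another could read it as covering pain drugs only.

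**Working it through.** The plan gives no figure on this point, so the check sets the statements side by side.

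1. **Scope of the ban.** The Intervention section names no class, dose or exception. No other section narrows the ban or permits background medicines.

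2. **Consequence.** The patient must discontinue involvement in the study, which goes further than stopping the plaster.

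3. **Who is eligible.** Because only severe cardiac or renal impairment is excluded, milder forms remain eligible. Hypertension and diabetes are not on the exclusion list either. A 70-year-old with mild cardiac disease on daily treatment can meet every listed criterion and still break the literal rule on the first day.

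4. **What screening catches.** Screening before randomization is made against the selection criteria, and none of these names medicines. The willingness criterion and informed consent would stop some patients on long-term medicines before randomization. They do not remove the safety concern, because one way to show willingness is to stop the medicine.

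5. **Whether the wording can be read more narrowly.** It can. The same section says "All drugs will be administered externally for 2 weeks", using the word drugs for the trial plasters. The Background gives a natural set of alternatives: "Pharmacologic treatments include oral analgesics, acetaminophen, ibuprofen, and traditional Chinese medicinal (TCM) products". A reader could take the ban to mean those. The first of these passages does not settle the matter, since a drug other than the plaster could be any drug at all.

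6. **Period.** The plaster is applied for 14 consecutive days and visits run to week 4. The rule's opening phrase could cover the treatment days alone or the whole follow-up, and the text does not say which.

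7. **Size.** The document does not give the share of patients on regular medicines. The Sample size section assumes 20% withdrawal but does not divide it by cause. The number affected therefore cannot be calculated, and it is zero if the narrow meaning was intended and applied.

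**The case against.** The strongest reply is that this is one loosely worded sentence in a condensed article. On that view the context points to osteoarthritis drugs, and lists of permitted and prohibited medicines belong in the full protocol, which is not shown. Part of this stands. The narrow meaning is plausible, and the absence of an itemised list is no fault. But the article states a rule and a penalty, and as worded they clash with its own entry criteria. The point concerns what is written.

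A second reply is that the willingness criterion is itself a selection criterion, so patients who cannot comply fail screening. This also stands in part. Most long-term users would probably be stopped there or at consent, which makes exit after randomization the less likely route.

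Three stronger readings are tempting, and the document does not support them:

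- **That the rule biases the primary comparison or costs power.** A reader might infer this because the Statistical analysis section fills dropouts by last observation carried forward. An early exit would indeed carry the baseline pain score forward and pull a true difference toward zero. But that holds for any dropout, and it needs patients who are enrolled despite the ban and then removed. The document does not say how many there would be. The number of visits filled after an exit is not evidence of impact.
- **That the plan tells patients to stop antihypertensives or similar medicines.** It does not say this. It follows only from the literal reading.
- **That exits after rescue analgesic use would differ between arms.** This is a separate question. The document gives no rates of such use, and the change proposed here keeps the ban on analgesics.

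**Conclusion.** The point holds as a minor one. The rule as written is wider than its evident purpose of keeping other pain relief out of the comparison, and it does not fit the entry criteria. Followed literally, it makes eligible patients on stable unrelated medicines stop them, decline entry or leave.

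This rests on two conditions: that at least one site applies the literal wording, and that some eligible patients take unrelated medicines. The document confirms neither. If the narrow meaning was intended and applied at all four hospitals, the effect is nil and only the wording needs correction. No size of bias or loss of power is claimed.

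**What to change.** In the Intervention section:

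- Limit the ban to analgesics, anti-inflammatories and other osteoarthritis treatments, including traditional Chinese medicine products for osteoarthritis.
- State whether the ban covers the 14 treatment days or the whole period to week 4.
- Expressly permit stable unrelated medicines, so that their users remain in the study, and record them.

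At the existing screening before randomization, check that each patient can comply with this same definition, at all four hospitals.

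The cost is a sentence or two of text and a brief medication check, with no new visit. Recruitment may be slightly slower. The downside is that unrelated medicines stay in the background of the blood, chemistry and urine tests listed under Safety assessments. Recording them lets those results and the adverse events be read with that in view.

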### Outcome measures

#### Primary outcome measure

The primary efficacy endpoint of the study will be the VAS, which is a pain score ranging from 0 mm (no pain) to 100 mm (worst pain ever experienced) [15]. Operationally, the VAS score is usually a horizontal line, 100 mm in length, anchored by word descriptors at each end. Patients mark the point on the line of current pain. The VAS score is then determined by measuring in millimeters from the left hand end of the line to the point that the patient marked. The VAS score will be measured during all the assessment visits (baseline and 1-, 2-, 3-, and 4-week follow-up).

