### Safety assessments

All subjects are to be questioned about adverse events during the treatment at each visit, and all adverse events reported will be analyzed, regardless of the investigators’ assessments of causality. Safety will be assessed by complete blood cell count, erythrocyte sedimentation rate, blood chemistry, and urinalysis.

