### Statistical analysis

The data will be collected and analyzed according to the intention-to-treat principle. Standard statistical techniques will be used to describe characteristics of patients in both groups. We will compare baseline characteristics in both groups and, if incomparability appears, we will perform a secondary analysis, adjusting for differences. The primary outcome will be compared between both groups using analysis of variance for repeated measures. All statistical analyses will be performed using SAS version 9.1 or a later version. All statistical tests will be two-sided and the level of significance will be set at 0.05. The last-observation-carried-forward method will be used to input data with dropouts. Continuous variables will be expressed as mean ± SD, and categorical variables as number and percentage [19]. If adjustment for possible baseline incomparability is needed, analysis of covariance will be performed [20].

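### Patients who take another drug must leave the study, which stops VAS collection and conflicts with collecting data by intention to treat

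*Protocol article*

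**What the plan says.** In the Intervention section, after the description of the placebo plaster, the protocol article states: "During the process, patients will not be allowed to use other drugs". The next sentence gives the consequence: "If they do so, patients are required to provide feedback to the investigators and discontinue involvement in the study". The period covered is not defined. No exemption is given for any class of drug, and the article does not describe any assessment after removal.

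The same section sets visits at baseline and at weeks 1, 2, 3 and 4, and says: "Assessments will be made during all five visits". The Primary outcome measure section places the VAS at each of these visits.

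The Statistical analysis section opens with: "The data will be collected and analyzed according to the intention-to-treat principle". It then specifies a repeated-measures analysis of variance for the primary outcome, and for missing data: "The last-observation-carried-forward method will be used to input data with dropouts". The Sample size section assumes 20% withdrawal, without dividing it by cause.

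**The concern.** Intention to treat asks for more than keeping everyone in the randomised arm at analysis. Its collection side, which this protocol names explicitly, means following patients for outcome whatever they do after randomisation. A rule that sends a patient out of the study for taking another drug does the opposite. It makes primary-outcome data missing by design, at visits that would otherwise have taken place.

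In a placebo-controlled pain trial, a patient who reaches for another drug may well have had poor relief. For such patients the unmeasured scores are plausibly related to outcome, and the frequency could differ between arms. The repeated-measures comparison would then use a carried-forward score at the later visits, or the baseline score at all of them if the patient left before the week 1 VAS. Later imputation or sensitivity analysis can only vary assumptions about those scores, because they were never observed. An analysis plan cannot recover data that the protocol stops collecting.

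**Working it through.** **Step 1: the rules side by side.** The plan gives no figure for other-drug use, so there is none to reproduce.

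- The removal rule (Intervention) ends the patient's part in the study. It does not say that only the plaster is stopped.
- The intention-to-treat statement (Statistical analysis) covers both collection and analysis.
- LOCF (Statistical analysis) fills the later visits for patients who drop out.

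The first and third are compatible on the analysis set: the patient leaves, stays in the randomised arm and is imputed. The first and second conflict on collection, because the rule stops measurement on account of a post-randomisation event.

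**Step 2: scores lost per removed patient.** Inputs:

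- Post-baseline VAS visits: weeks 1, 2, 3 and 4, so 4 per patient.
- Treatment: 14 days.
- Assumption: visit weeks are counted from the start of the plaster. This fits the statement "Used plasters will be reclaimed at the 1- or 2-week follow-up visit", although the article also describes the follow-up visits as coming after treatment.

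Let *k* be the week of the last VAS taken, with baseline as 0. Scores lost = 4 − *k*. For drug use in week *w*, exit before the next visit gives *k* = *w* − 1. Exit at the next visit, with its VAS taken, gives *k* = *w*.

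| Week of other-drug use | Exit before next visit: 4 − (*w* − 1) | Exit at next visit, VAS taken: 4 − *w* |
|---|---|---|
| 1 | 4 | 3 |
| 2 | 3 | 2 |
| 3 | 2 | 1 |
| 4 | 1 | 0 |

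**Step 3: ranges.**

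- Rule covers the 14 treatment days, exit by the next visit (rows 1 and 2): 2 to 4 of 4 lost.
- Rule covers all 4 weeks, exit by the next visit (all rows): 0 to 4 of 4 lost.
- Exit later than the next visit: fewer are lost. Use in week 2 that is disclosed only at week 4, with that VAS taken, gives *k* = 4 and 4 − 4 = 0 lost.
- Overall, therefore: 0 to 4 of 4 lost.

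**Step 4: the other visit clock.** If weeks 1 to 4 are counted from the end of treatment, the visits fall 3, 4, 5 and 6 weeks after plaster start. For use within the 14 days, exit before the first visit loses 4, and exit at the first visit with its VAS taken loses 3. The range is then 3 to 4 of 4, again provided exit is no later than the first visit.

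**The case against.** The strongest reply is that the plan is coherent as it stands. It expects withdrawals, sets a 20% rate for them, and says how dropouts are handled. On that view the conflict hangs on the mention of collection in one sentence, and the rest is a preference for observed over imputed data. The article is also condensed, and the authors may have meant only that the plaster stops.

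Part of this stands:

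- A reader might infer that removed patients are dropped from the analysis. The article does not say so; LOCF keeps them in.
- A reader might also see the VAS schedule as a contradiction in itself. It is not: any trial with withdrawals has both a schedule and a withdrawal rule.
- The absence of an exit-visit provision in a condensed article is not a fault. The point rests on what the sentence affirmatively requires.

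The rest does not answer the point. Collection is named in the protocol's own statement of principle, and imputation is not collection. If only stopping the plaster was meant, the wording still needs correcting, because sites will follow it as written. Allowing for 20% withdrawal protects numbers; it does not remove bias from outcome-related missingness.

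It is fair to add that scores taken after other-drug use reflect that drug too. How to treat them is an estimand choice, and collecting them leaves it open.

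**Conclusion.** The concern holds as a conflict over data collection, and it should be fixed. As written, the removal rule ends VAS collection for any patient who uses another drug, although the plan says data are collected by intention to treat. The reading of the 14-day or 4-week period does not change this.

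Per removed patient, 0 to 4 of the 4 post-baseline scores are lost, counting visits from plaster start. The narrower range of 2 to 4 needs two conditions: use within the 14 treatment days, and exit by the next visit. It is tempting to say that at least half the scores are always lost, but late disclosure can bring the loss to none.

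Further inferences that the document does not support:

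- **Number affected.** Applying the 20% to 320 gives 0.20 × 320 = 64 patients, but that rate is withdrawal from any cause. No rate of other-drug use is given.
- **Size or direction of bias.** Neither can be derived. The ban covers all other drugs, so not every removal need be related to pain.
- **Other data.** SF-36 loss depends on whether it follows the five-visit schedule, which its section does not state. Loss of adverse-event data is also conditional, since the Safety assessments section says: "All subjects are to be questioned about adverse events during the treatment at each visit".

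**What to change.** Reword the removal sentence in the Intervention section so that use of another drug may stop the plaster but does not end follow-up. Specifically:

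- Continue the scheduled assessments to week 4 for every randomised patient unless consent is withdrawn.
- Record the drug, date and reason for use.
- Use the observed scores in the intention-to-treat analysis, with a sensitivity analysis that handles scores after other-drug use differently. Which of the two is primary is for the sponsor to settle as an estimand choice.

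The cost is mainly protocol and case-report-form wording, since the visits are already scheduled. The downside is that later scores will include the effect of other drugs, which may narrow the difference between arms.
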